### Randomization

Ultimately, 180 participants will be randomized to the acupuncture treatment plus usual care group or usual care alone group and divided into four centers (see Figure 1). Each center will recruit a total of 45 participants, with 30 assigned to the acupuncture plus usual care group and 15 to the usual care alone group. A block size of 3 is used to assign 2 for acupuncture treatment plus usual care group and 1 for usual care alone group. Separate randomization table will be provided for each center.

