### Statistical methods and sample size

Analyses will be performed for two populations: 1) an intention-to-treat population consisting of all randomized participants with at least one measurable outcome report following acupuncture treatment (missing data will be replaced with last observation values); 2) a per protocol population including only participants without major protocol deviations. All data will be analyzed descriptively. All main analyses will be based on the intention-to-treat population. For primary and secondary outcome measures, the mean differences from baseline values to the end of treatment will be compared using two-sample t-test or Wilcoxon rank sum test. A trend test will also be performed using repeated measures analysis of variance. We adjusted for possible confounders using criteria of statistical significance.

All adverse events reported during the study will be included in the charts; then incidences of adverse events will be calculated. The percentage of the subjects with adverse events in each group will be calculated and compared with the chi-squared test or Fisher's exact test value.

Statistical analyses will be performed using the SAS statistical package program (ver. 9.1.3) and the level of significance will be established at α < 0.05. In calculating the sample size, we assumed a power of 90% and α value of 5%, in order to detect a hot flush score difference of 15.34 with a standard deviation of 26.5 drawn by two previous studies in Korea [24,41]. Therefore the acupuncture plus usual care and usual care alone group (2:1 allocation) will include 120 and 60 participants, respectively, allowing for a 20% withdrawal rate. This implies a sample size of 45 for each center, with 30 participants per acupuncture treatment plus usual care group and 15 per usual care alone group.

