### Data handling

Investigators will enter the information required by the protocol into the Case Report Forms (CRFs). Non-obvious errors or omissions are entered on data query forms, which will be returned to the investigational site for resolution.

The data from all centres are pooled and summarized with respect to demographic baseline characteristics, effectiveness and safety observations.

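### Free improvement: the primary test on change from baseline neither conditions on the baseline score nor carries a term for centre, the randomisation stratum; one prespecified ANCOVA would add precision at the same N

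*Protocol article*

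**What the plan says.** Four statements in the Protocol article bear on the point.

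- **Main comparison** (Statistical methods and sample size): for primary and secondary outcomes, "the mean differences from baseline values to the end of treatment will be compared using two-sample t-test or Wilcoxon rank sum test". The data collection schedule (Table 2) puts the end of treatment at week 4.
- **Further analyses** (same section): "A trend test will also be performed using repeated measures analysis of variance", followed by "We adjusted for possible confounders using criteria of statistical significance". No covariate is named, and the second sentence is not tied to a particular analysis.
- **Randomisation** (Randomization): "Separate randomization table will be provided for each center", and "A block size of 3 is used to assign 2 for acupuncture treatment plus usual care group and 1 for usual care alone group". Each of the four centres is to contribute 30 and 15 women, so centre is a design stratum.
- **Sample size** (Statistical methods and sample size): 90% power at a 5% level to "detect a hot flush score difference of 15.34 with a standard deviation of 26.5", 2:1 allocation and 20% withdrawal, giving 120 and 60. The text does not say whether 26.5 is the SD of the change or of the score itself.

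**The concern.** A two-group test on change uses the baseline score in one rigid way: it subtracts it with slope 1. When baseline and week-4 scores are imperfectly correlated and have similar spread, the best slope is below 1. Subtracting the full baseline then adds noise that a fitted slope would remove. The entry rule sets only a lower limit (a daily score above 10), so baseline scores may differ widely between women.

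Centre is fixed by design but appears in neither named test. If centres differ in mean change, the balanced allocation removes those differences from the true error of the treatment contrast, yet the unstratified standard error still contains them.

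The sentence on confounders does not close the gap. Selecting covariates by statistical significance may or may not bring in baseline or centre. It also makes the fitted model depend on the data.

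At stake is the precision of the main estimate, using data that the trial collects anyway.

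**Working it through.** **Inputs from the Protocol article:** difference 15.34, SD 26.5, power 90%, α 5% (taken as two-sided), allocation 2:1, withdrawal 20%, 120 + 60 randomised.

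**Assumptions, not in the document:** correlation r between baseline and week-4 score, 0.3 to 0.8; equal SDs at the two times; 26.5 is the SD of change; between-centre share of variance (ICC), 0 to 0.10.

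**1. The plan's own sample size.** Control group n = (1 + 1/2) × [26.5 × (1.960 + 1.282) / 15.34]² = 47.04, rounded up to 48, with 96 in the acupuncture group. Dividing by 0.80 gives 60 and 120. The stated 180 reproduces.

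**2. Power of the named t-test.** SE = 26.5 × √(1/96 + 1/48) = 4.68, so the noncentrality is 15.34 / 4.68 = 3.27. On the noncentral t distribution with 142 degrees of freedom, power is 90.2% (90.6% by normal approximation).

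**3. Adding the baseline score.** With common SD s, the change has variance 2s²(1 − r). The ANCOVA residual variance is s²(1 − r²). The ratio is (1 + r)/2, so the effective SD is 26.5 × √((1 + r)/2).

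| Assumed r | Variance ratio | Effective SD | Power at 96/48 | 95% CI half-width (normal) |
|---|---|---|---|---|
| change score | 1 | 26.50 | 90.2% | 9.18 |
| 0.3 | 0.65 | 21.36 | 98.1% | 7.40 |
| 0.5 | 0.75 | 22.95 | 96.4% | 7.95 |
| 0.7 | 0.85 | 24.43 | 94.2% | 8.47 |
| 0.8 | 0.90 | 25.14 | 92.9% | 8.71 |

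The one to four degrees of freedom spent on baseline and centre do not change these powers at the first decimal.

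**4. Sensitivity to equal SDs.** Let the week-4 SD be k times the baseline SD. The ratio becomes k²(1 − r²) / (1 + k² − 2rk). At r = 0.5:
- k = 0.5: 0.1875 / 0.75 = 0.25
- k = 1: 0.75 / 1 = 0.75
- k = 1.5: 1.6875 / 1.75 = 0.96

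The ratio stays below 1 in all three cases, but the size of the gain varies widely.

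**5. If 26.5 is the SD of the score.** The change SD is 26.5 × √(2(1 − r)) and the ANCOVA SD is 26.5 × √(1 − r²). At r = 0.3 these are 31.36 and 25.28, with power of 78.5% and 92.6%. At r = 0.5 they are 26.50 and 22.95, with power of 90.2% and 96.4%.

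**6. Adding centre alone** (normal approximation; within-centre SD = 26.5 × √(1 − ICC)).

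| Assumed ICC | Power without centre | Power with centre | Type I error without centre |
|---|---|---|---|
| 0 | 90.6% | 90.6% | 0.050 |
| 0.02 | 90.8% | 91.1% | 0.048 |
| 0.05 | 91.1% | 91.9% | 0.044 |
| 0.10 | 91.7% | 93.2% | 0.039 |

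The centre gain is at most about 1.5 percentage points in this range. Leaving centre out makes the test slightly conservative.

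**The case against.** The strongest reply is that nothing here is wrong. The test is valid under randomisation, the sample size follows from its inputs, and the trial has 90% power for the test it names. The plan also mentions adjustment for confounders and a repeated measures analysis. A condensed article may leave covariate lists and the rule for choosing a test to a fuller document. Most of this stands, and it limits the point to efficiency. It does not remove the point, because the article itself fixes the form of the main comparison and the basis for choosing covariates. The repeated measures analysis is described as an additional trend test, not as the main comparison.

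A reader might infer four stronger claims that the document does not support.

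- **That baseline is ignored.** It is subtracted; what is missing is an estimated slope.
- **That chance baseline imbalance biases the result.** Imbalance is random and already inside the t-test's standard error. With consistent inputs (SD 26.5, r = 0.5), a one-standard-error imbalance of 4.68 moves the change-score estimate by 0.5 × 4.68 = 2.3 points. That is the same cost as the lost precision, not a second one.
- **That the article orders centre to be left out of the primary test.** The sentence "The data from all centres are pooled and summarized with respect to demographic baseline characteristics, effectiveness and safety observations" stands under Data handling and concerns pooled summaries. It sets no rule for the primary test.
- **That the choice between t-test and Wilcoxon inflates false positives.** In simulations with assumed skewed data, always reporting the smaller p-value gave about 7%, but choosing by a normality test gave 4.7% to 5.1%. The first is a worst case that the article does not describe. An unstated choice rule is largely missing detail.

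**Conclusion.** The point holds as a free improvement. The named comparison does not condition on baseline and has no centre term, and the significance-based adjustment guarantees neither. Type I error is not inflated by these omissions, no bias follows, and the sample size of 180 is right for the plan's inputs.

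If 26.5 is the SD of change and SDs are equal at both times, baseline adjustment cuts the variance by 35% to 10% for r from 0.3 to 0.8. Power rises by about 8 to 3 percentage points. Centre adds roughly 0 to 1.5 points for an ICC of 0 to 0.10. The document gives neither r nor the ICC, so the direction of the gain is firmer than its size.

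**What to change.** - Make the single primary analysis a linear model of the week-4 hot flush score on arm, baseline score and centre. Report the adjusted mean difference with its 95% CI.
- Replace covariate selection by statistical significance with these prespecified terms.
- Keep a rank-based or log-scale analysis as a named sensitivity analysis for skewness, rather than as an alternative primary test.
- Use the same model for the Menopause Rating Scale, with its own baseline value as covariate.
- Leave N at 180.

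The cost is wording only. The baseline diary, the baseline Menopause Rating Scale and centre are all recorded already, and no visit, measurement or participant is added.

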**Methods:**

This study consists of a multi-center randomized controlled trial with 2 parallel arms. Participants included in the study will meet the following criteria: 1) a documented daily average hot flush score ≥ 10 for one week prior to the screening visit 2) not taking HRT and other pharmaceutical therapies which might affect hot flushes or other vasomotor symptoms.

While maintaining usual care, the treatment group will receive acupuncture 3 times a week, for a total of 12 sessions over 4 weeks. The control group will receive usual care alone during the same period. Post-treatment follow-up will be performed one month after completing 12 sessions of acupuncture.

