### Exclusion criteria

Participants will be excluded when they are suffering serious medical conditions, such as uncontrolled hypertension, diabetes mellitus requiring insulin injection, any type of thyroid dysfunction, past or current malignant tumor, severe dyslipidemia, other infectious diseases or systemic diseases insufficient for acupuncture treatment.

Ineligible participants will also include those who used any hormones, antidepressants, gabapentin, selective serotonin reuptake inhibitors (SSRI) or sedatives. In the case of previous or current use of HRT, adequate wash-out periods will be dictated according to the type of HRT (i.e. oral administration, transdermal patch or injection).

Over the counter (OTC) drugs will be allowed for managing episodic colds, headaches and dyspepsia, etc. Some supplements including evening promise oil, phytoestrogens, omega-3 fatty acids, calcium and vitamins will also be permitted; however, participants will be gently advised to reduce the dose, stop taking the supplement, or at least refrain from adding another supplement to their regimen. Some OTC drugs containing black cohosh and human placenta extracts will not be allowed since there are concerns that those herbs might directly affect hot flushes and other vasomotor symptoms, in certain constitutions, according to Traditional Korean Medicine (TKM) theory. We will investigate the drugs taken by each participant at every visit and request that study participants notify us of any addition to their medication/supplement regimen. Any additional acupuncture treatment, herb prescription, or therapeutic intervention by another TKM doctor will not be allowed during the study. For the purpose of analyzing daytime and nighttime hot flushes separately, we will exclude participants who work at night. See eligibility criteria in table 1.

**Table 1 T1:** Eligibility Criteria

Inclusion criteria
45–60 years old
Perimenopausal women (menstrual irregularity or amenorrhea of 3 – 11 months)
Postmenopausal women:
- 12 months of spontaneous amenorrhea
- 6 months of spontaneous amenorrhea with serum FSH levels > 40 mIU/ml
- 6 weeks postsurgical bilateral oophorectomy with or without hysterectomy
- hysterectomy with at least one intact ovary
Average daily hot flash scores > 10 for one week prior to screening visit

Exclusion criteria

Poorly controlled hypertension
Diabetes mellitus needed to be controlled by insulin injection
History of past or current malignant tumor

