### Study outcome

The primary outcome measure is the hot flush score, produced by multiplying severity and frequency of hot flushes during a 24-hour period in a daily diary, which demonstrates validity and reliability in measuring hot flush activities [27]. Participants will be asked to record the number and severity of daily hot flushes during the entirety of the study period. Participants in both groups will also be routinely encouraged to fill out the diary by periodic short message service (SMS) and phone-call reminder both in order to avoid the selective loss to follow up, that is, selection bias and to prevent the indolence of writing daily diaries which are associated with participant knowledge-related bias in this unblinded trial. We will employ the slightly modified severity rating scale (0:none, 1:mild, 2:moderate, 3:severe, 4:very severe) suggested in the studies of Sloan et al. [27].

We will examine the reduction in hot flushes over a 24-hour period, as well as daytime and nighttime separately for sub-analytic purpose to check whether acupuncture has different effects on daytime versus nighttime hot flushes.

The secondary outcome measure is the Menopause Rating Scale (MRS) to assess other vasomotor symptoms. MRS is a highly qualified self-administered questionnaire for assessment of menopausal symptoms [37]. It contains 11 questions divided into 3 categories: psychological, somatic and urogenital.

We will also estimate the expectations of participants by using the credibility and expectancy questionnaire, aiming to determine whether expectations make a difference to outcome [38,39]. In order to assess expectations without potential influences by participants' knowledge of allocation results, a questionnaire will be administered to eligible women before notification of assignments. Data collection schedule is detailed in table 2.

**Table 2 T2:** Data Collection Schedule

Measures	Screening	Baseline Randomization				End		Follow-up
Week number	-1	0	1	2	3	4	6	8

Sociodemographic characteristics	O							
Hot flush diary	O	O	O	O	O	O	O	O
Credibility and Expectancy questionnaire		O						
MRS		O		O		O	O	O
Medical history	O							
Physical activity	O							
Smoking/Alcohol	O							
Pharmaceutical therapies (OTC and prescribed drugs)	O	O	O	O	O	O		O
Herb medications	O	O	O	O	O	O		O
Adverse effects			O	O	O	O		
FSH, Estradiol	O							
TSH, Free T4	O							

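### The stated primary test cannot use the two pre-randomisation hot flush diary scores as covariates; a covariance analysis with both would probably be more precise at almost no cost

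*Protocol article*

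**What the plan says.** - **Primary comparison.** Under Statistical methods and sample size, for primary and secondary outcomes, "the mean differences from baseline values to the end of treatment will be compared using two-sample t-test or Wilcoxon rank sum test". The section also mentions a repeated measures trend test and an adjustment for variables picked by statistical significance. The baseline hot flush score is not named as a covariate, and the baseline is not tied to particular diary days.
- **Entry.** The abstract requires "a documented daily average hot flush score ≥ 10 for one week prior to the screening visit". Each woman therefore has a weekly diary mean by the time of screening.
- **Schedule.** In Table 2 (Study outcome), the row "Hot flush diary" is marked at screening (week -1), at week 0, which is headed as baseline and randomisation, and at every later visit. The text above the table asks for daily recording throughout.
- **Sample size.** The trial is sized to "detect a hot flush score difference of 15.34 with a standard deviation of 26.5", with 90% power and 5% alpha, so that the arms ("2:1 allocation) will include 120 and 60 participants, respectively") are obtained after "allowing for a 20% withdrawal rate".

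**The concern.** Hot flush scores vary between women and, within a woman, from week to week. An unadjusted change score subtracts the whole baseline value, noise included. A covariance analysis subtracts only the part that predicts the outcome. A second pre-randomisation week can improve that prediction if part of the weekly variation is noise.

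Both scores precede randomisation, so neither can be affected by allocation, and the entry cut-off applies to both arms alike. Using them creates no bias between arms. What is at stake is the width of the confidence interval for the primary effect, not the validity of the test.

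**Working it through.** **1. Reproduce the plan's figure.** Inputs from Statistical methods and sample size: difference 15.34, SD 26.5, alpha 0.05 (two-sided assumed, because it reproduces the stated total), power 0.90, allocation 2:1, withdrawal 20%.

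Control n = 1.5 × [26.5 × (1.960 + 1.282) / 15.34]² = 47.04, rounded up to 48. Acupuncture n = 96, so 144 are evaluable. Dividing by 0.8 gives 60 and 120, total 180, as stated. Power at 48/96 by the noncentral t is 90.2%.

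**2. Set up the comparison.** Assume that 26.5 is the SD of change from one baseline week (the article does not say) and that weekly variances are equal and set to 1. Write r1 = corr(week -1, week 0), r4 = corr(week 0, week 4) and r5 = corr(week -1, week 4). The article gives none of these. Variances:

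- change from week 0: 2 − 2·r4
- change from the mean of both weeks: 1 + (1 + r1)/2 − (r4 + r5)
- covariance analysis, week 0 only: 1 − r4²
- covariance analysis, both weeks: 1 − (r4² + r5² − 2·r1·r4·r5)/(1 − r1²)

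**3. Results.** Columns A to C are variances relative to change from week 0. Column D is two covariates relative to one (C/B).

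| Assumed r1 / r4 / r5 | A: change from two-week mean | B: one covariate | C: two covariates | D: C/B |
|---|---|---|---|---|
| 0.5 / 0.5 / 0.5 | 0.75 | 0.75 | 0.67 | 0.89 |
| 0.6 / 0.6 / 0.6 | 0.75 | 0.80 | 0.69 | 0.86 |
| 0.7 / 0.7 / 0.7 | 0.75 | 0.85 | 0.71 | 0.83 |
| 0.8 / 0.8 / 0.8 | 0.75 | 0.90 | 0.72 | 0.80 |
| 0.8 / 0.6 / 0.5 | 1.00 | 0.80 | 0.80 | 0.998 |
| 0.9 / 0.6 / 0.55 | 1.00 | 0.80 | 0.80 | 0.999 |
| 0.9 / 0.6 / 0.5 | 1.06 | 0.80 | 0.79 | 0.987 |
| first-order autoregressive, 0.9 per week | 1.02 | 0.83 | 0.83 | 1.00 |
| first-order autoregressive, 0.95 per week | 1.04 | 0.91 | 0.91 | 1.00 |

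Worked example, 0.9 / 0.6 / 0.5. Change: 2 − 1.2 = 0.80. Two-week mean: 1 + 0.95 − 1.1 = 0.85, and 0.85/0.80 = 1.06. One covariate: 1 − 0.36 = 0.64, and 0.64/0.80 = 0.80. Two covariates: 1 − (0.36 + 0.25 − 0.54)/0.19 = 0.632, and 0.632/0.80 = 0.79.

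**4. Translate to power at 48/96.** Two covariates at ratio 0.91 give SD 26.5 × √0.91 = 25.3 and power about 93%. At ratio 0.67 the SD is 21.7 and power about 98%. The two-week mean gives SD 22.95 and 96.4% in its best case (0.75), and SD 27.3 and about 88% in its worst case (1.06).

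**5. When averaging helps.** The two-week mean beats the single week only if r4 − r5 < (1 − r1)/2. It fails when the older week predicts the outcome clearly less well and the two baseline weeks are already highly correlated.

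**The case against.** **The baseline may already include both weeks.** A reader might infer that the primary change uses week 0 alone and that the screening diary serves only as an entry check. The article does not say so. That reading rests on a column heading in Table 2 that names a visit, and on silence elsewhere. A condensed article may also leave the baseline window to the full protocol or analysis plan. This stands, so the point does not rely on that reading. What the article does fix is the test, and neither named test can take either diary score as a covariate.

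**Nothing is broken.** The sample size reproduces exactly, and an unadjusted change score is a valid, unbiased comparison. This stands, and is why the point is only an optional improvement.

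**The gain is assumed, not shown.** It would be tempting to say that free precision is being lost, or that variance would fall by 25%. That figure belongs to averaging under equal correlation between all weeks, its best case. With decaying correlation, averaging gains nothing or loses a little. The second covariate can also add close to nothing: any gain beyond one covariate depends largely on how much of the weekly variation is independent noise, which the article does not report. This stands in full for averaging. For covariates it limits the second week's share but not the gain from adjustment itself.

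**The screening week is selected.** The entry cut-off truncates it, which may weaken its correlation with later weeks. Averaging it into the baseline could also bring regression to the mean into each arm's reported reduction. Neither effect differs between arms. Both are further reasons to prefer covariates to averaging.

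**Conclusion.** The point holds as an efficiency improvement of low severity. The article commits the primary comparison to a test that cannot adjust for hot flush scores it already schedules before randomisation. It gives the screening-week score no analytic role.

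Over the cases examined, a covariance analysis with both weekly means has about 9% to 33% lower variance than the planned change score. The second week itself contributes about 0% to 20% relative to one baseline covariate. These ranges assume that 26.5 is the SD of change from one week, that weekly variances are equal, and that correlations lie in the ranges tabulated. None of this is given in the article. In large samples the second covariate cannot raise the residual variance; its cost is one degree of freedom, about 0.7% at 144 evaluable participants (1/144).

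The documents do not support saying that the trial is underpowered or that its sample size is wrong.

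**What to change.** In Statistical methods and sample size, replace the t-test or Wilcoxon comparison for the primary outcome with a pre-specified covariance analysis of the end-of-treatment hot flush score (or its change; with week 0 in the model the treatment estimate is the same). Enter the screening-week mean and the week-0 mean as two separate covariates, included whatever their statistical significance. State which diary days form each mean.

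Do not average the two weeks into a change-score baseline by default. If a change score is kept, check the between-week correlations first, ideally in the two earlier Korean studies used for the sample size.

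Cost: this changes the named primary method, so it should be settled before outcome data are seen. It needs a short rewrite of the analysis text, one degree of freedom per covariate (one more for the second week), no new data, and no change to the 180 participants.

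### Covariates are to be chosen by statistical significance, and the plan does not say whether the adjusted or the unadjusted comparison decides

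*Protocol article*

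**What the plan says.** All the relevant text is in the Protocol article, Statistical methods and sample size.

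- Primary and secondary outcomes, as change from baseline to end of treatment, "will be compared using two-sample t-test or Wilcoxon rank sum test".
- Next comes "A trend test will also be performed using repeated measures analysis of variance".
- The sentence directly after that is "We adjusted for possible confounders using criteria of statistical significance". It gives no covariate list, threshold or model, and does not limit the choice to variables measured before randomisation.
- On significance, "the level of significance will be established at α < 0.05".
- The only stated ranking is "All main analyses will be based on the intention-to-treat population". This fixes the population, not the method.
- The sample size is set to "detect a hot flush score difference of 15.34 with a standard deviation of 26.5" at 90% power and 5% alpha. With this, the groups "2:1 allocation) will include 120 and 60 participants, respectively, allowing for a 20% withdrawal rate".

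**The concern.** There are two linked problems.

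The first is the selection rule, which is weak on either reading.

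- **Significance of differences between arms.** Randomisation makes the null hypothesis true, so a significant difference is a chance finding. The rule then adjusts for variables that may not predict the outcome and leaves out ones that do.
- **Significance of association with the outcome.** The model is fixed only after the outcome is seen. In this trial the outcome is a self-reported diary score from participants who know their allocation.

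The second is the missing ranking. A two-sample t-test or Wilcoxon test takes no covariates, so any adjusted result is a further analysis beside it. If the two fall on opposite sides of 0.05, the article does not say which is the trial's result. What is at stake is the credibility of the primary claim, and the 5% error rate if the choice is left until the results are known.

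**Working it through.** **1. The plan's own figure.** Inputs: difference 15.34, SD 26.5, power 90%, alpha 5%, allocation 2:1, withdrawal 20%.

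Controls = (1 + 1/2) × (z_alpha + z_power)² × (SD/difference)²

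- Two-sided 5%: 1.5 × (1.960 + 1.282)² × (26.5/15.34)² = 47.04, so 48 controls and 96 treated. Dividing by 0.8 gives 60 and 120, exactly as stated. Power at 48/96 is 90.6% (normal approximation).
- One-sided 5%: 39 controls, 49 after withdrawal. This does not match.

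The size therefore rests on one unadjusted two-sided 5% comparison of means.

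**2. Error rates with no treatment effect.** Simulation with 96 versus 48 evaluable participants, 10,000 null trials per scenario, normal data and a nominal 5% level. Each cell spans the results for 5 and 10 candidate covariates. The article gives no covariate strength, so the joint R² of the candidates with the change score is an assumption, varied from 0 to 0.4. Monte Carlo standard error is about 0.2 to 0.3 points.

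| Rejection rate (%) | R² = 0 | R² = 0.2 | R² = 0.4 |
|---|---|---|---|
| t-test alone | 4.9–5.4 | 4.7–4.9 | 4.8–5.0 |
| Fixed covariate list alone | 4.9–5.3 | 4.7–5.3 | 4.7–5.3 |
| Selected by outcome association, alone | 4.9–5.3 | 4.8–5.0 | 4.7–5.3 |
| Selected by arm imbalance, alone | 5.0–5.3 | 4.2–4.4 | 3.8–3.9 |
| t-test or outcome-selected model | 5.1–5.8 | 6.7–6.9 | 7.6–8.2 |
| t-test or imbalance-selected model | 5.2–5.7 | 5.1–5.5 | 5.4–5.5 |
| t-test, Wilcoxon or outcome-selected model | 5.9–6.6 | 7.5–7.6 | 8.3–9.1 |

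A second simulation set the baseline–outcome correlation at 0.5 and also used skewed scores. It gave 7.2% to 8.2% for the t-test or the outcome-selected model, and 8.4% to 10.2% when Wilcoxon was added.

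**3. Where the excess comes from.** With the baseline score as the only real predictor (correlation 0.5 with the outcome), two ways of having a second chance were compared: the t-test or a significance-selected model, and the t-test or a fixed ANCOVA on baseline score. One run gave 7.2% and 7.1%. Another gave 7.6% for both. A fully pre-specified covariate produces the same excess, so the cause is the open choice between two results, not the selection step.

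**4. Analytic check.** Under the null, the t-test and a fixed adjusted test have statistics that correlate at about √(1 − R²). For R² = 0.2 this is √0.8 = 0.894, and the bivariate normal chance that at least one exceeds 1.96 in absolute value is 7.1%. For R² = 0.4 it is √0.6 = 0.775, giving 8.0%. Both agree with the simulation.

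**The case against.** The best defence is that the article already points to a main comparison. It ties the primary and secondary outcomes to the t-test or Wilcoxon test, says the trend test is done in addition, and sizes the trial on unadjusted means. The adjustment sentence follows the repeated measures analysis and may apply only to that. An explicit ranking might also sit in an analysis plan that is not shown.

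Much of this stands. The unadjusted comparison is the likelier main analysis, and the adjustment may be confined to the repeated measures model. But the text settles neither point. The significance criterion is also a rule that the article states, not a detail that it leaves out.

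A reader might infer three stronger things that the document does not support.

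- **That selecting by significance breaks the 5% level.** Used alone, the selected model stays near 5%, or somewhat below it with imbalance-based selection.
- **That every outcome certainly gets a rival adjusted result for the same change score.** This is one reading. The article describes no such model.
- **That the error rate is about double.** The figures near 9% to 10% require the t-test and the Wilcoxon test both to be run and the better result kept, with the adjusted model as a third chance. The wording reads more naturally as alternatives chosen by distribution.

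**Conclusion.** The point holds as a fault in a stated rule plus an unsettled ranking, and should be corrected. It is not a demonstrated breach of the 5% level.

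- Covariate selection by significance is unsuitable here on either reading. Used alone it gives a type I error of about 4% to 5%.
- If the t-test or the adjusted result could be claimed, the rate is about 5% to 8%. The low end applies to weak covariates or imbalance-based selection, the high end to outcome-based selection with R² near 0.4.
- The upper extreme of about 9% to 10% needs the further assumption that the t-test and Wilcoxon test are both run and the better one is kept.

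These figures rest on assumed covariate strength, 96 and 48 evaluable participants, and a choice between results that the article leaves open but does not announce.

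**What to change.** Before the data are seen:

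1. Delete the statistical-significance criterion.
2. List a few baseline covariates already collected, for example baseline hot flush score, and centre, by which randomisation is done. Keep them in the model whether or not they are significant.
3. Name one analysis of the change in hot flush score to end of treatment as the deciding test at two-sided 5%.
4. Label all other adjusted, rank-based and repeated measures analyses as supportive, unable to replace the deciding test.

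With one pre-specified analysis the simulated error rate is 4.7% to 5.4%. The cost is about two sentences, with no extra data or participants, and 120 and 60 stand because they rest on an unadjusted comparison. The downside is that a variable that happens to look imbalanced can be adjusted for only in a sensitivity analysis.
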